### Withdrawal of patients

A patient must be withdrawn from the trial (i) at any time at the patient’s own request, (ii) after salvage therapy if the patient fails to obtain CR/Cri/CRh, (iii) at any time if unacceptable toxicity necessitating cessation of treatment is observed, (iv) at any time if there are changes in the medical status of the patient that compromise the patient’s safety or if the investigator considers that the withdrawal is in the patient’s best interest, (v) in case of pregnancy, (vi) at any time a patient’s protocol compliance turns out insufficient, and (vii) if patient is lost to follow-up.

If any of the aforementioned criteria are met, and patients agree to follow-up, previous unresolved AEs will continuously be followed. If cases iii and iv are met we will continue with the follow-up of the patient until the end of the study. However, if the patient withdraws from the trial and also from consent for disclosure of future information (e.g., follow-up visits), further data collection is prohibited.

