### Treatments and study procedures

#### Salvage therapy

All patients are randomized upfront and receive one cycle of backbone salvage therapy with a standard HAM regimen. In patients aged 18–60 years, one cycle of cytarabine 3g/m^2^ every 12 h will be administered intravenously on days one to three, and in patients older than 60 years of age, cytarabine will be administered at a reduced dosage of 1g/m^2^ bidaily on days one to three. Mitoxantrone will be administered irrespective of age group, intravenously at a dosage of 10mg/m^2^ on days two and three. All patients will receive in addition 40 mg of quizartinib orally on days 1 to 28. If on day 28 no hematological recovery has occurred, and according to the first bone marrow examination no CR is achieved, quizartinib may be given until day 42 and a second remission control can be done if medically justified until day 42. If a therapy with a strong CYP3A4 inhibitor is initiated, a dose reduction of quizartinib to 20mg per day will be initiated. Dose modifications in case of toxicities are described in Tables 1 and 2.

**Table 1 Tab1:** Dose reduction or interruption of quizartinib

Nonhematological events grade 3 related to quizartinib and persisting > 48 h without resolution to ≤ grade 2	Dosing will be interrupted for up to 14 days. If the AE resolves to ≤ grade 1 within 14 days, the subject may resume dosing at the reduced dose of at least 50%.
Grade 4 toxicity at least possibly due to study drug	Treatment will be discontinued
Myelosuppression CRp or CRi	Dose may be reduced without interruption if the following criteria are met: Subject has received a minimum of 2 cycles of ASP2215, platelets < 25 × 10^9^/L and/or ANC ≤ 0.5 × 10^9^/L, marrow blasts < 5%, no evidence of extramedullary disease, further dose reduction is permitted if dosing 1 full cycle at the reduced dose has not resulted in the desired hematologic recovery.

*Abbreviations: AE*, adverse event; *ANC*, absolute neutrophil count; *CRi*, complete remission with incomplete hematologic recovery; *CRp*, complete remission with incomplete platelet recovery

**Table 2 Tab2:** Dose reduction or interruption of quizartinib in case of QTcF prolongation

QTcF >480 ms ≤500 ms	The dose of quizartinib will be reduced by at least 50%without interruption of dosing. Following dose reduction, the quizartinib dose may be resumed at the previous level in the next cycle if the QTcF has decreased to within 30 ms of baseline or <450 ms.

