#### Long-term follow-up

After EOT, all patients move to the observational follow-up with 3-monthly visits. For patients of the MRD-triggered arm, safety follow-up starts after the last visit of the last cycle of chemotherapy with subsequent transition to observational follow-up until the end of the study (EOS).

After the end of the study visit, patients are routinely followed-up and treated as per the standard of care at the discretion of the treating physician. Follow-up is planned to continue until the last patient alive has been observed for at least 2 years in total (study treatment including subsequent follow-up). Assuming 2 years of recruitment, the total observation period of the first patient may last up to 4 years. Event-free and overall-survival follow-up is recorded until the end of the overall study.

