### Efficacy endpoints

The primary endpoint of the study is the achievement of CR, Cri, or CRh after salvage therapy with HAM in combination with quizartinib. CR is defined as bone marrow blasts <5%, absence of circulating blasts and blasts with Auer rods, absence of extramedullary disease, neutrophil count ≥1000/μl, and platelet count ≥100,000/μl. CRi is defined as CR with residual neutropenia (neutrophils < 1000/μl) or thrombocytopenia (platelets < 100 000/μl) and CRh is defined as a CR with partial recovery of peripheral blood counts with residual neutropenia (neutrophils < 500/μl) or thrombocytopenia (platelets < 50,000/μl).

Refractory disease or treatment failure is defined as failure to achieve CR, Cri, or CRh, presence of Auer rods, or appearance of new or worsening extramedullary disease after one course of intensive treatment. Relapse after CR, CRi, or CRh is characterized by ≥5% blasts in the bone marrow aspirate and/or biopsy not attributable to any other cause, the reappearance of leukemic blasts in the peripheral blood, the new appearance of extramedullary leukemia, or presence of Auer rods. Platelet and neutrophil counts for the assessments of CR, CRi, and CRh are delineated based on the 2017 recommendations from the International Working Group commissioned by the European Leukemia Net [26].

Secondary survival endpoints are event-free survival (EFS), defined from randomization until one of the following events, whichever occurs first: (a) failure to obtain CR or CRi or CRh after Q-HAM therapy, (b) relapse from CR/Cri/CRh, or (c) death from any cause. Patients without an event are censored at the last follow-up. Overall survival (OS) is defined as the time from randomization until death from any cause and relapse-free survival (RFS) is measured from the first CR/Cri/CRh to the time of recurrence of the disease or death from any cause, whichever occurs first. Patients without event are censored at the last date of follow-up. Cumulative incidence of relapse (CIR) is defined as the time from the achievement of a CR/CRi/CRh after salvage therapy to the recurrence of the disease, whereby death from any cause is a competing event. Cumulative incidence of death (CID) is defined as the time from the achievement of a CR/CRi/CRh after salvage therapy to death from any cause whereby recurrence of the disease is a competing event.

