For the analysis of the primary endpoint, a logistic regression model will be applied to assess the odds ratio of CR/CRi/CRh rate after salvage therapy for patients receiving Q-HAM versus matched controls not receiving Q-HAM. The null hypothesis H0: OR≤1 is tested against its alternative H1: OR>1 at a one-sided significance level of *α*=0.05. The logistic regression analysis will be adjusted for age, high-risk cytogenetics (yes/no), and CR1 duration <18 months (yes/no/not applicable due to refractory disease). Due to the adaptive nature of the trial, two separate logistic models will be fitted for the two trial stages and be combined using the inverse normal function approach. Determination of *p*-values, point, and interval estimates will take the adaptive nature of the trial into account. Concerning the secondary endpoints: EFS, OS, and RFS endpoints will be analyzed using a Cox regression model and Kaplan-Meier plots, CIR, and CID will be analyzed according to Gray 1988 [33] and via cumulative incidence plots, and quality of life will be analyzed descriptively according to the corresponding guidelines and EORTC recommendations. Safety endpoints will be analyzed descriptively. Analyses of the primary and secondary endpoints will be based on the full analysis population (all randomized patients with treatment groups assigned in accordance with the randomization, regardless of the treatment actually received (intention to treat (ITT)). For patients with incomplete follow-up, time to last follow-up date will be used as the censoring time in the analysis of time-to-event data. Otherwise, no imputation of missing data will be conducted. For the biometricians, patient treatment shall remain blinded from the time of randomization until the final database lock. The interim analysis and sample size recalculation will be conducted by an independent biometrician who is not involved in the conduct of the trial. Statistical analysis will be performed using SAS v9.4 or higher [34].

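### The sections on withdrawal and on follow-up conflict over whether salvage non-responders are followed for survival, leaving overall survival open to informative censoring

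*Protocol article*

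**What the plan says.** All statements are in the protocol article.

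- **Withdrawal of patients.** Seven situations oblige withdrawal from the trial. Case ii is "after salvage therapy if the patient fails to obtain CR/Cri/CRh" and case vi is insufficient compliance. For any withdrawn patient who agrees to follow-up, "previous unresolved AEs will continuously be followed". Then: "If cases iii and iv are met we will continue with the follow-up of the patient until the end of the study". Cases iii and iv are unacceptable toxicity and a change in medical status or the patient's best interest. Data collection is forbidden only where the patient also withdraws consent to future information.
- **Long-term follow-up.** All patients enter three-monthly observation after end of treatment (EOT), and "Event-free and overall-survival follow-up is recorded until the end of the overall study".
- **Ancillary and post-trial care.** Observation ends for all patients on one study-wide date, 730 days after day 1 of the last included living patient. EOT is placed after maintenance cycle 12 (prophylactic arm) or consolidation cycle 2 (MRD-triggered arm, no cross-over).
- **Efficacy endpoints.** "Overall survival (OS) is defined as the time from randomization until death from any cause". Failure to respond to salvage is itself an event for event-free survival (EFS).
- **Sample size calculation and statistics.** Analysis is by intention to treat in all randomized patients. With incomplete follow-up, "time to last follow-up date will be used as the censoring time".

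**The concern.** The withdrawal section is the only text written for withdrawn patients, so a site handling a salvage failure would naturally turn to it. There it finds mandatory withdrawal, adverse-event follow-up, and observation to study end for two named cases that do not include this one. The general follow-up text points the other way, but it starts at EOT, and no EOT is defined for a patient who stops after one salvage cycle.

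If the site stops collecting survival data, the patient's overall survival (OS) time is censored at withdrawal. Kaplan-Meier and Cox methods assume that censored patients have the same later risk as those who remain. That is implausible here: the Discussion cites response to salvage as a strong survival covariable (P<0.0001). The OS curve beyond the assessment would then describe responders while being reported for all randomized patients, and many deaths would go unobserved.

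**Working it through.** The article states no OS rate, event count or OS power, so there is no figure to reproduce. The calculation shows the size of the effect if the withdrawal rule is applied as written.

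**Inputs from the article**
- Response rate p: 0.55 planned, 0.30 for controls (Sample size calculation and statistics).
- Maximum enrolment: 80.
- Time of assessment: day 28. The Salvage therapy section allows a later one ("If on day 28 no hematological recovery has occurred" and there is no CR) up to day 42. Non-responders are therefore withdrawn at about four to six weeks.

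**Assumptions (not in the article)**
- Exponential survival from randomization, with median m_R for responders and m_N for non-responders, shown over a range.
- Non-responders still alive are censored at w = 42/30.4375 = 1.38 months.
- All other patients are followed for at least 24 months.

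**Numbers affected.** Non-responders: 80 × (1 − 0.55) = 36, or 80 × 0.70 = 56 if the drug adds nothing. Alive at day 42: 36 × 2^(−1.38/m_N), which is 28.3 for m_N = 4, 30.7 for 6 and 32.4 for 9.

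**Formulas.** With S_R(t) = 2^(−t/m_R) and S_N(t) = 2^(−t/m_N):
- Full follow-up: S(12) = p·S_R(12) + (1 − p)·S_N(12).
- Non-responders censored at w: the Kaplan-Meier curve tends to [p·S_R(w) + (1 − p)·S_N(w)] × S_R(12)/S_R(w).

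**Worked case, p = 0.55, medians 18 and 4 months**
- Full: 0.55 × 0.630 + 0.45 × 0.125 = 0.403.
- Censored: (0.55 × 0.948 + 0.45 × 0.787) × 0.630/0.948 = 0.876 × 0.664 = 0.582.
- Overestimate: 17.9 points.

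**12-month OS, full follow-up versus day-42 censoring**

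| Medians R/N (months) | p = 0.55 | Excess (points) | p = 0.30 | Excess (points) |
|---|---|---|---|---|
| 18/4 | 0.40 vs 0.58 | 17.9 | 0.28 vs 0.56 | 27.9 |
| 12/4 | 0.33 vs 0.47 | 13.6 | 0.24 vs 0.45 | 21.1 |
| 12/6 | 0.39 vs 0.48 | 9.5 | 0.33 vs 0.47 | 14.8 |
| 9/6 | 0.33 vs 0.39 | 5.7 | 0.29 vs 0.38 | 8.8 |
| 9/9 | 0.40 vs 0.40 | 0 | 0.40 vs 0.40 | 0 |

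Censoring at day 28 instead gives 6.0 to 19.4 points at 0.55 and 9.3 to 30.2 at 0.30, again zero for 9/9. A simulation of 400,000 patients per scenario, with administrative censoring uniform over 24 to 48 months, agrees with these probabilities to within 0.003.

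**Deaths observed.** In the same simulation at p = 0.55, across the four scenarios where response is prognostic, deaths per 80 patients fall from about 68–76 with full follow-up to about 40–46 with day-42 censoring.

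**The case against.** The strongest reply is that the article already provides for survival follow-up. The sentence on survival recording has no exception and is not tied to EOT, observation ends for everyone on one date, and the analysis is by intention to treat. The withdrawal section never says that survival status is not collected in case ii; it is silent, and it bars data collection only on withdrawal of consent. The full protocol, which is not shown, may settle this. That stands as far as it goes: a reader might infer that non-responders are in fact censored at six weeks and that OS is therefore overestimated, and the documents do not support that as fact. What they show is a conflict. It remains because naming two of seven cases for observation to study end would be pointless if all were meant, and because the route into observation starts at an EOT that a non-responder never reaches.

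Three further inferences should be resisted.
- *The primary result or EFS is damaged.* It is not: non-response is a failure in the first and an event in the second.
- *The comparison with historical controls fails.* The matched comparison is specified for CR/CRi/CRh; no OS comparison with those controls is stated.
- *The randomized comparison is tilted.* Both arms receive the same treatment through salvage, so censoring of non-responders should be similar by arm and no bias towards either is expected. The Discussion sets the randomized objective in terms of EFS.

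It is also fair that every median is assumed, and that deaths before assessment remain observed OS events. The calculation allows for the latter by starting survival at randomization.

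Finally, Trial status reports early closure with 11 patients. The figures per 80 describe the design as planned, so the practical gain from an amendment is now small. At p = 0.55, though, 11 × 0.45 is about 5 non-responders, and the OS reported for those enrolled still depends on which rule was applied.

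**Conclusion.** The point holds as an unreconciled contradiction with a conditional bias. The sections on withdrawal, long-term follow-up and post-trial care disagree on survival follow-up of salvage non-responders. If the withdrawal rule is followed, censoring is informative and 12-month OS is overestimated by about 6 to 18 points at a response rate of 0.55, and about 9 to 28 points at 0.30. These ranges rest on exponential survival, day-42 censoring and medians that the article does not give. The overestimate is zero if response carries no prognostic information or if the general follow-up text governs. The damage is confined to the level of one secondary endpoint, any outside comparison of that level, and the number of deaths observed. It should be fixed, but it does not undermine the primary analysis. Case vi raises the same ambiguity; its size was not estimated.

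**What to change.** Reconcile Withdrawal of patients, Long-term follow-up and Ancillary and post-trial care:

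1. Define withdrawal from study treatment and withdrawal from follow-up as separate events.
2. State that patients withdrawn under cases ii and vi, like those under iii and iv, remain in survival follow-up until the end of the study unless they withdraw consent to data collection.
3. Say when observational follow-up begins for a patient who stops after salvage, since the present EOT definition does not reach that patient.

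No treatment rule changes. The cost is a short amendment and a survival-status contact at the three-monthly interval already planned. Given the early closure, the equivalent step for patients already enrolled is to obtain survival status where consent allows, and to report how many non-responders were censored at withdrawal. Status not collected at the time may be hard to recover later.

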### Treatments and study procedures

#### Salvage therapy

All patients are randomized upfront and receive one cycle of backbone salvage therapy with a standard HAM regimen. In patients aged 18–60 years, one cycle of cytarabine 3g/m^2^ every 12 h will be administered intravenously on days one to three, and in patients older than 60 years of age, cytarabine will be administered at a reduced dosage of 1g/m^2^ bidaily on days one to three. Mitoxantrone will be administered irrespective of age group, intravenously at a dosage of 10mg/m^2^ on days two and three. All patients will receive in addition 40 mg of quizartinib orally on days 1 to 28. If on day 28 no hematological recovery has occurred, and according to the first bone marrow examination no CR is achieved, quizartinib may be given until day 42 and a second remission control can be done if medically justified until day 42. If a therapy with a strong CYP3A4 inhibitor is initiated, a dose reduction of quizartinib to 20mg per day will be initiated. Dose modifications in case of toxicities are described in Tables 1 and 2.

**Table 1 Tab1:** Dose reduction or interruption of quizartinib

Nonhematological events grade 3 related to quizartinib and persisting > 48 h without resolution to ≤ grade 2	Dosing will be interrupted for up to 14 days. If the AE resolves to ≤ grade 1 within 14 days, the subject may resume dosing at the reduced dose of at least 50%.
Grade 4 toxicity at least possibly due to study drug	Treatment will be discontinued
Myelosuppression CRp or CRi	Dose may be reduced without interruption if the following criteria are met: Subject has received a minimum of 2 cycles of ASP2215, platelets < 25 × 10^9^/L and/or ANC ≤ 0.5 × 10^9^/L, marrow blasts < 5%, no evidence of extramedullary disease, further dose reduction is permitted if dosing 1 full cycle at the reduced dose has not resulted in the desired hematologic recovery.

*Abbreviations: AE*, adverse event; *ANC*, absolute neutrophil count; *CRi*, complete remission with incomplete hematologic recovery; *CRp*, complete remission with incomplete platelet recovery

**Table 2 Tab2:** Dose reduction or interruption of quizartinib in case of QTcF prolongation

QTcF >480 ms ≤500 ms	The dose of quizartinib will be reduced by at least 50%without interruption of dosing. Following dose reduction, the quizartinib dose may be resumed at the previous level in the next cycle if the QTcF has decreased to within 30 ms of baseline or <450 ms.
QTcF >500 ms	Quizartinib dosing will be interrupted for up to 14 days. • If QTcF returns to within 30 ms of baseline or <450 ms within 14 days, quizartinib administration may be resumed at a reduced dose. If QTcF >500 ms occurs during the Induction or Consolidation Phases, and if no cause other than quizartinib can be identified, then during the maintenance phase, the dose of quizartinib cannot be escalated to 60 mg/day.
QTcF >500 ms or >60 ms change from baseline, and Torsade de pointes or polymorphic ventricular tachycardia or signs/symptoms of serious arrhythmia	Quizartinib dosing will be permanently discontinued.

*Abbreviations: QTcF*, corrected QT interval by Fredericia

Subjects who experience QT interval prolongation of more than 480 ms corrected for heart rate (QTcF) will undergo dose interruption and/or reduction of quizartinb and will be monitored closely by ECGs, performed twice weekly for the first week of the QTcF prolongation and then weekly thereafter until the QTcF prolongation is resolved (Table 2). QTcF prolongations higher than grade 3 according to the National Cancer Institute Common Terminology Criteria for Adverse Events (CTC AE) will be recorded as adverse events of special interest (AESI) including the Investigator’s assessment of seriousness, causality, and a detailed narrative.

In the event of significant toxicity grade 3 or 4, dosing must be interrupted, delayed, and/or reduced by at least 50% [20]. In the event of unresolved or severe toxicities, administration will be interrupted and in case of multiple toxicities, dose modification should always be based on the worst toxicity observed. Quizartinib will be discontinued in case of non-hematological grade 4 toxicities including grade 4 QTcF prolongation.

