Common adverse events (AEs) observed in the phase I and II studies included gastrointestinal disorders (nausea, diarrhea, and vomiting), hematologic disorders (anemia, neutropenia, and thrombocytopenia), febrile neutropenia, fatigue, and QT prolongation.

Although hematologic toxicity is associated with the underlying disease, safety reports from Study AC220-002 in AML indicate delayed recovery or continued suppression of absolute neutrophil counts (ANC) and platelets as a consequence of continued treatment with quizartinib [20].

Based on phase I and phase II studies’ results, it appears reasonable and clinically feasible to combine salvage therapy with quizartinib in patients with r/r- *FLT3*-ITD mutated AML. This manuscript describes the rationale, design, and dosing details of the Q-HAM study (clinicaltrials.gov identifier NCT03989713; EudraCT No 2018-002675-17), a phase II study comparing quizartinib adjunct to salvage therapy to historical controls based on the matched threshold crossing approach.

The primary objectives of the study are (i) to assess the clinical efficacy of quizartinib in combination with high-dose cytarabine and mitoxantrone and (ii) to assess the clinical efficacy of MRD-triggered and preemptive quizartinib continuation therapy in patients with r/r- *FLT3*-ITD mutated AML.

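### Table 1 and the salvage-therapy text set different stopping rules for grade 4 toxicity, with different strictness for a possibly related grade 4 cytopenia

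*Protocol article*

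**What the plan says.** All the dosing rules at issue are in the Protocol article.

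- **Salvage therapy, Table 1, grade 3 row.** This row is expressly limited by toxicity type and by attribution: "Nonhematological events grade 3 related to quizartinib and persisting" beyond 48 hours.
- **Salvage therapy, Table 1, grade 4 row.** The trigger is "Grade 4 toxicity at least possibly due to study drug" and the action is discontinuation. Attribution is a condition; toxicity type is not.
- **Salvage therapy, Table 1, myelosuppression row.** For patients in CRp or CRi with low counts, the dose may be lowered without a break, on the condition "Subject has received a minimum of 2 cycles of ASP2215".
- **Salvage therapy, text after Table 2.** A general sentence reads "In the event of significant toxicity grade 3 or 4, dosing must be interrupted, delayed, and/or reduced by at least 50" percent. The closing sentence of that paragraph reads "Quizartinib will be discontinued in case of non-hematological grade 4 toxicities including grade 4 QTcF prolongation". Here toxicity type is a condition and attribution is not.
- **Salvage therapy, main text.** Salvage is one cycle. Quizartinib runs to day 28 and may run to day 42 if counts have not recovered and the first marrow shows no CR.
- **Continuation therapy.** Readers are sent to Tables 2 and 3 for dose modifications. Table 3 lists eligibility criteria.

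**The concern.** A site using the table and a site using the text could treat the same event differently. The case that matters is grade 4 cytopenia. The Background names "hematologic disorders (anemia, neutropenia, and thrombocytopenia), febrile neutropenia, fatigue, and QT prolongation" among the common adverse events of quizartinib, and safety reports from an earlier phase II study describe "continued suppression of absolute neutrophil counts (ANC) and platelets as a consequence of continued treatment with quizartinib". In this trial the drug is given with high-dose cytarabine and mitoxantrone, so a grade 4 cytopenia that an investigator cannot rule out as drug-related is foreseeable. Followed to the letter, Table 1 takes such a patient off quizartinib. The text asks for no more than interruption, delay or reduction.

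The choice can also bear on trial participation. Under Withdrawal of patients, a patient leaves the trial "at any time if unacceptable toxicity necessitating cessation of treatment is observed". A row that orders cessation for an expected effect makes that clause easier to reach than the text does.

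**Working it through.** No figure in the plan depends on this point, so the check sets the two rules side by side. A grade 4 event is classed by two features: whether it is hematological, and whether it is at least possibly due to study drug. That gives 2 × 2 = 4 cases.

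| Grade 4 event | Table 1, grade 4 row | Text after Table 2 | Same stop decision? |
|---|---|---|---|
| Hematological, possibly related | Discontinue | Interrupt, delay or reduce; stopping not required | No |
| Hematological, unrelated | Not triggered | Stopping not required | Yes |
| Non-hematological, possibly related | Discontinue | Discontinue | Yes |
| Non-hematological, unrelated | Not triggered | Discontinue | No |

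As written, the rules differ in 2 of 4 cases. Two charitable readings can be tried:

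1. Read the Table 1 row as non-hematological only. The first case is resolved and the last remains: 1 of 4.
2. Read toxicities in the text as drug-related only. The last case is resolved and the first remains: 1 of 4.
3. Adopt both readings together: 0 of 4.

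The article states neither reading. The first is harder to assume because the row directly above carries the non-hematological limit and the grade 4 row does not.

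Could the myelosuppression row settle the first case by taking cytopenia out of the grade 4 row? Not during salvage. It needs CRp or CRi and at least 2 cycles of treatment, whereas salvage is a single cycle. For a grade 4 cytopenia in that cycle, the grade 4 row is the only row of Table 1 that could apply.

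Two smaller slips sit in the same rules. The 2-cycle condition refers to ASP2215, a code that the article never defines and uses nowhere else, in a table titled for quizartinib. Taken literally, the condition does not refer to the trial drug. The citation of Tables 2 and 3 under Continuation therapy leaves out Table 1 and points to the eligibility table; the salvage section cites Tables 1 and 2 correctly.

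**The case against.** The strongest reply is that the intended meaning can be worked out. The grade 3 row is non-hematological, myelosuppression has its own row, the main text foresees dosing to day 42 without count recovery, and the text after Table 2 supplies the missing word. On this view the grade 4 row is a loose shortening of the text. Likewise, the discontinuation sentence sits among rules for drug toxicity, so a relatedness condition may be implied. This carries weight as evidence of intent, and it supports the direction of the fix. It does not remove the discrepancy: both unstated readings are needed, and the myelosuppression row does not reach the salvage cycle. Non-recovery at day 28 also need not be grade 4.

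A reader might infer that the two places give opposite instructions. They do not. The text never forbids stopping for a hematological grade 4 event. Its general sentence on grade 3 or 4 toxicity sets a minimum action, since the same paragraph goes on to require discontinuation for part of that group. The rules differ in strictness.

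A reader might also infer harm to the primary analysis, because the section on post-randomization events sets the response to missing for patients who withdraw before it is measured. The article does not show this. The withdrawal clause turns on unacceptable toxicity, not on the Table 1 row itself, and patients withdrawn under it are to be followed to the end of the study. Nor is any rate of possibly related grade 4 cytopenia given, so the number of patients affected cannot be estimated.

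Finally, this is an article and the full protocol is not shown, so whether sites worked under the same conflict is unknown. That limits what can be said about conduct. It does not excuse the article, which prints both rules; nothing here is an omission through condensing.

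**Conclusion.** The point holds as a wording inconsistency with safety relevance. On a literal reading the table and the text reach different stop decisions in 2 of 4 grade 4 cases. The important one is the possibly related cytopenia, where Table 1 requires discontinuation and the text requires less. The other, an unrelated non-hematological event, rests on reading the text sentence without an implied relatedness condition and is weaker. The conclusion relies only on the printed wording and on the Background's own account of count suppression under quizartinib.

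No effect on the primary endpoint, sample size, significance level or power is shown. Practical reach is small: Trial status reports 11 patients and a decision to close early. The stray code is a real error in a dosing condition; the table citation is clerical. The correction is worth making because the rule is wrong as printed and costs almost nothing to put right.

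**What to change.** 1. In Table 1, put the word non-hematological in front of "Grade 4 toxicity at least possibly due to study drug". This matches the grade 3 row and the text.
2. In the discontinuation sentence after Table 2, add the same relatedness condition that the Table 1 row uses, so that one attribution rule applies in both places.
3. State that hematological grade 4 toxicity is handled by interruption, delay or reduction, worded so that it fits the option to continue quizartinib to day 42 when counts have not recovered.
4. In the myelosuppression row, replace ASP2215 with quizartinib.
5. Under Continuation therapy, cite Tables 1 and 2 for dose modifications.

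The cost is an edit to two table rows, the dose-modification text and one citation. Sample size and analysis do not change.
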